### Statistical analyses

The endpoint event in the present study will be assessed using the concept of intention-to-treat (ITT). In the event that no differences in incidence of adverse events or functional outcomes are found at 90 days when comparing the experimental and control groups, our team will proceed onto a phase-2 trial.

The Kolmogorov–Smirnov test for normality and the equal variance will be conducted prior to any other statistical analysis methods. For continuous variables with normal distribution, a 2-sided *t* test for independent samples will be applied in order to detect differences between the groups. A Mann–Whitney U test will be performed for continuous variables that have a non-normal distribution. For categorical variables, χ2 or Fisher exact tests will be used when fitting. A *p* value of < 0.05 will be the threshold to determine statistical significance. Statistical analysis will be performed on SPSS 22.0.

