### Randomization and blindness

The participants will provide consent and assigned randomly in a 1:1 (*n* = 40) fashion to the two treatment groups with the use of computer-generated randomization. Interventionalists, outcome assessors, and investigators involved in data collection and analysis for the trial will be blinded to this assignment with the use of opaque envelopes.

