### Interventions

Stroke patients that satisfy inclusion criteria will be assigned randomly to either the control group or experimental group. All patients will also receive standard stroke treatment, including antiplatelet or anticoagulation medications, antihypertensive medications, hyperlipidemia and hyperglycemia control, and neurotrophic treatment. In experimental group, 800 μg NTG will be diluted using 10 cc isotonic NaCl solution administered via catheter over 10 min after vessel recanalization. The control group will receive 10 cc isotonic NaCl administered via the catheter over 10 min.

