### Outcomes and assessment procedures

Participant demographic information, stroke risk factors, occlusion site, and procedure of mechanical thrombectomy will be recorded. On hospital admission, ASPECTS (Alberta Stroke Program Early CT Score) and NIHSS (National Institute of Health stroke scale) scores will be determined and recorded for further analysis. Magnetic resonance imaging (MRI) or computerized tomography (CT) will be completed 24 h after mechanical thrombectomy. NIHSS and mRS scores will also be determined at baseline and at 24 h, day 7, 14, and 90 after stroke onset.

*Primary Outcomes (Safety Assessment)*. The primary safety consideration of AGAIN is the risk of symptomatic intracranial hemorrhage (ICH). The secondary safety outcomes include: 1) episodes of hypotension requiring clinical treatment during GTN administration; 2) neurological deterioration is defined as NIHSS score increasing more than 4 point from baseline to day 7; 3) ICH, fatal ICH; 4) death regardless of cause during the study period; 5) headache, tachycardia, emesis, and seizures.

*Secondary Outcomes (Efficacy Assessment)*. The main parameter to assess efficacy of AGAIN is functional independence on day 90 post-intervention (as determined by scores between 0 to 2 on the mRS scale, which are representative of functional independence), infarct volumes, NIHSS scores, and blood nitrate index detection [cyclic guanosine monophosphate (cGMP), L-arginine, and L-citrulline)]. The infarct volume is measured using the Siemens Syngo with Diffusion-Weighted Imaging (DWI) by the image tool (ROI) (this is done by outlining the infarcted area on each section in order to calculate the area and subsequently by multiplying this value from each layer by its respective thickness).

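### Patients randomised to GTN but never infused would dilute the intention-to-treat harm comparison towards the no-difference result that triggers phase 2; a safety set by infusion received should stand beside it (cheap improvement, low severity)

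*Protocol article*

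**What the plan says.** All of this is in the protocol article.

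- Statistical analyses, analysis principle: "The endpoint event in the present study will be assessed using the concept of intention-to-treat (ITT". No other analysis set is named there.
- Statistical analyses, next sentence: "In the event that no differences in incidence of adverse events or functional outcomes are found at 90 days" between the arms, the team goes on to a phase-2 trial.
- Outcomes and assessment procedures: "The primary safety consideration of AGAIN is the risk of symptomatic intracranial hemorrhage (ICH". The secondary safety outcomes include hypotension that needs treatment during GTN administration, neurological deterioration, any and fatal haemorrhage, death, headache, tachycardia, emesis and seizures.
- Interventions: "800 μg NTG will be diluted using 10 cc isotonic NaCl solution administered via catheter over 10 min after vessel recanalization". The control arm receives saline by the same route over the same time.
- Statistical analyses, tests: "For categorical variables, χ2 or Fisher exact tests will be used when fitting", and "A *p* value of < 0.05 will be the threshold to determine statistical significance".

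**The concern.** When the aim is to show a difference, intention-to-treat is the cautious choice, because patients who do not get their assigned treatment pull the arms together and make success harder. Here the favourable result is the absence of a difference in harms, so the same pull makes a favourable result easier.

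A patient assigned to GTN who receives none of it cannot be harmed by it, but still counts in the GTN denominator. This is plainest for hypotension during GTN administration, an event that a patient who was never infused cannot have. At stake is a phase-2 decision, for a use of the drug on which the sample-size section says it has no reference data, that could lean on a comparison partly made up of unexposed patients.

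**Working it through.** **Inputs from the article.** Patients are "assigned randomly in a 1:1 (*n* = 40) fashion to the two treatment groups". The sample-size section gives 40 as the total, so there are 20 per arm: 2 × 20 = 40, the upper end of its range of 10 to 20 per group. That section gives no power, effect size or event rate, so there is no power figure to reproduce.

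**Assumptions not in the article.** Event risks p1 (GTN, if infused) and p0 (control); the number k of the 20 GTN patients who are never infused; that those k patients carry the control risk; and a two-sided Fisher test (the article states two-sidedness only for the t test).

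**Step 1: expected difference.** The intention-to-treat risk in the GTN arm is [(20 − k) × p1 + k × p0] / 20. Subtracting p0 gives (p1 − p0) × (20 − k)/20. So k = 1, 2 and 4 shrink the difference by 5%, 10% and 20%. For 20% v 5%, 15 points become 15 × 19/20 = 14.25, 15 × 18/20 = 13.5 and 15 × 16/20 = 12.0 points.

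**Step 2: chance of seeing the harm.** The GTN count is the sum of a binomial(20 − k, p1) and a binomial(k, p0), and the control count is binomial(20, p0). Adding the probabilities of all outcome pairs with Fisher p < 0.05 gives:

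| Assumed risk, GTN v control | k = 0 | k = 1 | k = 2 | k = 4 |
|---|---|---|---|---|
| 10% v 5% | 0.017 | 0.015 | 0.014 | 0.011 |
| 20% v 5% | 0.168 | 0.150 | 0.133 | 0.102 |
| 30% v 5% | 0.446 | 0.409 | 0.372 | 0.298 |
| 50% v 10% | 0.742 | 0.699 | 0.651 | 0.547 |

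**Step 3: set this against the sample size.** The chance of a no-difference finding is one minus the power. At 20% v 5% it is 0.832 with everyone infused and 0.867 with two uninfused, a rise of 0.035. At 30% v 5% it goes from 0.554 to 0.628, a rise of 0.074. With no control events, 5 GTN events are needed for p < 0.05 (p = 0.047); with one control event, 7 are needed (p = 0.044). Most of the false reassurance is therefore already there at k = 0.

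**Step 4: what a safety set restores.** Dropping the k uninfused patients removes the shrinkage in Step 1. For k = 2, computed Fisher power is 0.232 at 20% v 5% and 0.506 at 30% v 5%. Both exceed the fully infused 20 v 20 values (0.168 and 0.446). Fewer patients cannot carry more information about the same risks, so part of that gap comes from the discreteness of Fisher's test with 18 v 20. These power figures should not be read as the gain from the fix. The gain is that the estimate is no longer diluted.

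**The case against.** The case against is substantial, and most of it limits the point.

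- A reader might infer that intention-to-treat is the only analysis and covers every endpoint. The article does not say so. It has one short sentence about the endpoint event and does not rule out a supporting safety set, which the full protocol or analysis plan may define. What stands is the published pairing of that principle with a go rule that rewards a null result on harms.
- A reader might infer that infusions stopped early also dilute the harm in a way that a safety set would cure. They are outside this point. A partly infused patient belongs in the GTN arm under both approaches. A pressure fall that needed treatment during the infusion is already a counted event, and removing such patients could hide harm.
- A reader might fault the article for not listing the volume infused among the recorded items. Such detail is commonly left to the full protocol and case report form, so its absence here shows nothing.
- Non-receipt is probably uncommon. Patients are enrolled after endovascular therapy; lack of recanalization and systolic pressure below 120 mmHg before GTN are exclusions; and treatment is a single 10-minute infusion. This stands, with one reservation: the article does not say whether randomisation comes before or after the pressure check, so some never-infused patients remain possible.
- Reading non-significance at 20 per arm as safety is the larger weakness. That also stands. Non-receipt adds a second, smaller error in the same direction.

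**Conclusion.** The point holds as a conditional one. If patients randomised to GTN go uninfused, the stated analysis moves the harm comparison towards the outcome that triggers phase 2, in proportion to the uninfused fraction. At one patient in 20 the effect is slight (5% of the difference). At two it costs about 0.035 to 0.09 of power in the scenarios from 20% v 5% to 50% v 10% (0.168 − 0.133 = 0.035; 0.742 − 0.651 = 0.091), and almost nothing at 10% v 5%, where power is negligible anyway. These sizes rest on assumed event risks, an assumed number uninfused, and the assumption that the uninfused carry the control risk.

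The document does not support saying that GTN harms will be understated, because it gives no non-receipt rate. Low severity: a cheap improvement.

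**What to change.** Keep intention-to-treat as stated. For the primary and secondary safety outcomes, add a safety set of patients in whom the study infusion was started, analysed by the infusion actually received. Partly infused GTN patients stay in the GTN arm, with their events also listed separately. State that the phase-2 decision must hold in both analyses. If the full protocol or analysis plan already defines such a set, it is enough to tie the decision rule to it.

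The cost is a sentence or two in the analysis section and one extra set of tables. The safety set may lose a patient or two and is not fully protected by randomisation, which is why intention-to-treat stays beside it. The change does nothing for the low power at 20 per arm.

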### Estimation of sample size

Intra-catheter administration of GTN in AIS patients after mechanical thrombectomy is our first attempt to address the effect of GTN in AIS patients with endovascular therapy. There is no data available for reference. AGAIN is a pilot study to examine the study design, methods, procedures, inclusion criteria, and operational strategies. The results will be used to estimate the sample size and conduct a power analysis for a phase-2 trial. Based on two other protocols published in Frontiers in Neurology [25, 26], 10 to 20 participants per group may be adequate to assess the initial safety and feasibility trends of intra-catheter administration of GTN. Therefore, a similar number of sample of total 40 patients was selected in this pilot study.

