
The neuroprotective effect of NO donors has been found to prevent ischemia–reperfusion (I/R) injury after AIS in preclinical studies [18]. GTN is one of the most extensively used exogenous NO donors clinically, but its application after endovascular recanalization has not been reported yet. Transdermal and sublingual GTN has failed to confer improvements in functional outcome in AIS patients [19–23]. The neuroprotective effect of NO donors are suggested to be consistently dependent on the dose, location, source and environment [24]. Due to cascade expansion of inflammatory responses during the whole process of I/R injury, early intra-arterial administration of GTN after vessel recanalization (during the early stage of I/R injury) may be the best method to prevent ischemic-reperfusion injury and exert its clinical neuroprotective benefits. Additionally, arterial administration of GTN has been demonstrated to be neuroprotective in MCAO animal model [24]. Therefore, it is possible that intra-arterial administration of GTN after vessel recanalization would most effectively enable this compound to reach target sites and have the greatest therapeutic effect. We will determine the safety of intra-arterial GTN and its prospective ability to improve functional outcomes in patients who suffer an AIS. This sequence may best enable us to assess the benefits and clinical transformation of GTN and mechanical thrombectomy in AIS patients.

There are certain limitations of the proposed study. First, the trial will be conducted at single center and has a small sample size, which may influence the generalizability of the conclusions that may be drawn and potentially invites illegitimate results to the study. Second, the target dosage of GTN still needs optimization in the context of its use after mechanical thrombectomy. The dose of GTN was decided according to the coronary artery research in which 200-500ug GTN was given through a catheter [37–39] and clinical experience of GTN used in cardiovascular and cerebrovascular diseases intervention therapy.

AGAIN proposes to ascertain the safety, feasibility, and, secondarily, the efficacy of intra-arterial GTN combined with mechanical thrombectomy in patients who suffer an AIS. The preliminary data will provide the parameters for clinical trials in the future.

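### The rule for moving to phase 2 takes the absence of a significant difference in 20 v 20 patients as the go signal, and it has no direction

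*Protocol article*

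**What the plan says.** The progression rule is one sentence in Statistical analyses. If "no differences in incidence of adverse events or functional outcomes are found at 90 days" between the two groups, then "our team will proceed onto a phase-2 trial". The rule gives no margin, maximum event rate, confidence bound or direction. The same section lists t, Mann–Whitney, chi-square and Fisher tests and says a p "value of < 0.05 will be the threshold to determine statistical significance". No other criterion for a difference is given.

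The sample size is 40, randomized 1:1. Estimation of sample size bases it on precedent from two other protocols, saying that "10 to 20 participants per group may be adequate to assess the initial safety and feasibility trends", and gives no power or precision calculation. Outcomes and assessment procedures names sICH as the primary safety consideration, lists death among the secondary safety outcomes, and makes functional independence (mRS 0–2) at day 90 the first-listed efficacy measure. Background states the hypothesis that GTN may benefit these patients.

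**The concern.** The rule has two faults, both in text that the article itself fixes.

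First, a test that fails to reach p < 0.05 shows that two arms are alike only if it could have detected a difference that matters. At 20 per arm, with uncommon events, it mostly could not. Read with the section's only criterion, the rule turns low power into a go signal.

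Second, the rule covers functional outcomes without saying which direction counts. A significant improvement on GTN, which is what the trial hypothesises, is a difference and so does not satisfy the condition.

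At stake is whether more patients are given the regimen in a phase-2 trial. That decision would rest on a criterion that can be met despite a large excess of the primary safety event.

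**Working it through.** **Nothing to reproduce.** The total of 40 comes from precedent, so there is no calculation of the plan's own to check. What can be checked is how the rule behaves at 20 v 20.

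**Inputs**
- n = 20 per arm (40 in total, 1:1): Randomization and blindness; Estimation of sample size.
- Significance level 0.05: Statistical analyses. Two-sided is stated there for the t test and assumed here for the categorical tests.
- Test for binary outcomes: chi-square or Fisher, Statistical analyses. Both are shown; chi-square is uncorrected.
- Background functional independence 46% and mortality 15.3%: Background. Used as control rates.
- Control sICH rate: not in the article. Assumed 5%, with a range of 2% to 10%.

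**Method.** For true rates p_T and p_C, the probability of a significant result is the sum, over all 21 × 21 tables (a, b) with test p < 0.05, of Bin(a; 20, p_T) × Bin(b; 20, p_C). One minus this sum is the chance of declaring no difference on that endpoint.

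**Harm, one endpoint at a time**

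| Outcome | Control → GTN | Detected, Fisher | Detected, chi-square | Missed, Fisher / chi-square |
|---|---|---|---|---|
| sICH (assumed 5%) | 5% → 10% | 1.7% | 5.4% | 98% / 95% |
| | 5% → 15% | 7.0% | 15.4% | 93% / 85% |
| | 5% → 20% | 16.8% | 29.2% | 83% / 71% |
| | 5% → 25% | 29.9% | 44.4% | 70% / 56% |
| Death | 15.3% → 30.6% | 12.8% | 20.9% | 87% / 79% |
| Independence | 46% → 36% | 5.3% | 9.3% | 95% / 91% |
| | 46% → 26% | 17.6% | 26.4% | 82% / 74% |

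For control sICH rates of 2% to 10%, a doubling is missed at least 92% of the time with Fisher and at least 86% with chi-square.

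**Which observed results would pass.** With Fisher, 4/20 v 0/20 gives p = 0.106 and 6/20 v 1/20 gives p = 0.091, so both would count as no difference; significance needs at least 5 v 0 or 7 v 1. Uncorrected chi-square is less conservative: 6 v 1 gives p = 0.037. The verdict on the same data therefore depends on which test is used.

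**Precision.** With 0/20 events, the exact two-sided 95% upper limit is 1 − 0.025^(1/20) = 16.8%.

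**Benefit.** Independence in 16/20 on GTN v 9/20 on control gives p = 0.048 (Fisher) or 0.022 (chi-square). The condition is then not met. With a control rate of 46%, the chance of a significant result is:
- true rise to 61%: 8.6% (Fisher), 14.2% (chi-square)
- to 66%: 15.1%, 23.1%
- to 76%: 38.2%, 49.8%

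The larger the true benefit, the less likely the go condition is met.

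**The case against.** The strongest reply is that the miss rates describe one endpoint, while the rule asks for no difference in adverse events and in function. A regimen that quadrupled sICH would probably also shift any ICH, neurological deterioration, death or mRS. This stands. The joint probability of passing can be no higher than the single-endpoint figure and would in practice be lower. It cannot be computed without assumptions about how the outcomes move together. A reader might infer that the rule sends a harmful regimen to phase 2 most of the time, or that a pass is almost certain even with large harm. The documents do not support either: the first needs the joint rate, and the second does not fit a chi-square miss rate of 56% at 5% v 25%.

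A reader might also infer that the plan forbids progression if GTN helps. It does not say so. The sentence states when the team will proceed and is silent on the alternative. Given the hypothesis, no worse is probably what was meant. Even so, this is the only go condition stated, and a significant benefit falls outside it. The text should say what is meant.

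This is a pilot that claims only initial trends. The Discussion concedes the small sample, an unaffiliated physician and the ethics committee monitor safety, and the decision is only to run another trial. These points lower the severity, and the size of 40 is not at fault. But the small sample is discussed in terms of generalizability and possibly unreliable results, without reference to the progression rule. An aim of looking at trends also argues for estimation over a significance gate.

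**Conclusion.** The point holds: the progression sentence is wrong as written and should be fixed. Failure to find a significant difference at 20 per arm is weak evidence of safety. Per endpoint, a rise in sICH from 5% to 20% is missed 83% (Fisher) or 71% (chi-square) of the time, and a doubling of death from 15.3% is missed 87% or 79% of the time. Separately, the lack of direction leaves a significant functional benefit with no stated route to phase 2.

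The conclusion rests on reading differences found as p < 0.05, which is the section's only criterion although the sentence does not repeat it. It also rests on two-sided categorical tests and, for sICH, on an assumed control rate; a doubling goes mostly undetected across 2% to 10%. The death and function figures use the article's own background rates as control rates.

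Two further criticisms might be drawn from the same sentence, and neither is supported. Adjusting for multiple tests would make harm harder to detect, which works against the main point. The absence of feasibility criteria from the rule is detail that a condensed article may leave to the full protocol.

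**What to change.** Reword the progression sentence in Statistical analyses so that:
- **It is directional.** Only a signal of worse safety or worse function counts against progression; benefit does not.
- **p < 0.05 is not the gate.** The decision rests on observed counts and rates in each arm and on their difference, with exact 95% confidence intervals. These are judged against a maximum acceptable sICH and death rate, or difference from control, that the sponsor sets and justifies in advance.
- **Non-significance is not described as evidence of safety.** The precision at n = 20 is stated, for example that 0/20 events still leaves a 95% upper limit of 16.8%.

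The cost is wording, plus the work of justifying the limits. The statistical downside is that any limit stops some acceptable regimens. As an illustration only, take a limit of at most 2/20 sICH in the GTN arm. A drug with no effect on sICH is stopped with probability 1 − P(X ≤ 2), X ~ Bin(20, p): about 8%, 32% or 60% of the time at background rates of 5%, 10% or 15%. Such a limit also ignores the control arm. The sponsor should therefore choose its own limit, show how it behaves over a plausible range of background rates, and read it alongside the between-arm difference.

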**Methods:**

AGAIN, a prospective RCT, is proposed for AIS patients after mechanical thrombectomy. Subjects will be randomly assigned in a 1:1 fashion (*n* = 40) to either the control group or the intervention group. Participants assigned to the intervention group will be administered 800 μg GTN in the catheter immediately after recanalization, whereas those in the control group will be administered the same volume of normal saline. All participants from either group will be given concurrent treatment with standard of care therapies in accordance with the current guidelines for stroke management. The primary outcome is safety [symptomatic intracranial hemorrhage (ICH), hypotension, neurological deterioration, ICH, fatal ICH, as well as headache, tachycardia, emesis, and seizures], whereas secondary outcomes included changes in poststroke functional outcomes, infarction volumes, and blood nitrate index detection.

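### The named efficacy tests are all unadjusted, and a normality pre-test picks between two of them, although baseline NIHSS and ASPECTS are recorded: the comparisons are unbiased but less precise than they need be

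*Protocol article*

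**What the plan says.** Statistical analyses fixes the methods. A Kolmogorov–Smirnov "test for normality and the equal variance will be conducted prior to any other statistical analysis methods". Continuous outcomes judged normal get a two-sided independent-samples t test and the others a Mann–Whitney test. Categorical outcomes get chi-square or Fisher, with significance at p < 0.05. No named test includes a covariate.

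Outcomes and assessment procedures states that admission ASPECTS and NIHSS "scores will be determined and recorded for further analysis". It heads the efficacy outcomes with "functional independence on day 90 post-intervention (as determined by scores between 0 to 2 on the mRS scale", and also lists infarct volume, NIHSS and blood markers. The primary outcome is safety, so efficacy is secondary.

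Estimation of sample size gives no power calculation: "a similar number of sample of total 40 patients was selected in this pilot study", on the ground that "10 to 20 participants per group may be adequate to assess the initial safety and feasibility trends". It also gives the purpose of the data: "The results will be used to estimate the sample size and conduct a power analysis for a phase-2 trial".

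Randomization and blindness describes 1:1 assignment "with the use of computer-generated randomization" and names no stratification factor.

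**The concern.** Two features of the named analysis deserve a change.

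- **No baseline adjustment.** Patients may enter with an NIHSS anywhere from 6 to 25 and an ASPECTS from 6 to 10. Such scores would be expected to predict later NIHSS and infarct volume. A crude comparison leaves that variation in the error term. With 20 per arm and no stratification named, chance differences at baseline pass straight into the estimates.
- **A data-driven choice of test.** The pre-test decides whether a mean difference or a rank comparison is reported. The quantity handed to the phase-2 planners is therefore not known in advance, and the two summaries are not interchangeable in a sample-size formula.

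At stake is the precision and usability of the pilot's efficacy estimates. The validity of the trial is not in question.

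**Working it through.** **The plan's own figure.** There is no formula to reproduce. The total of 40 is 2 × 20, the upper end of the 10 to 20 per group cited. No effect size, SD or power is stated, so every effect size, correlation and distribution below is an assumption. Common inputs are 20 per arm and two-sided 0.05.

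**1. Baseline adjustment of a continuous outcome.** With correlation r between baseline and outcome, the residual variance is multiplied by 1 − r², and the effective number per arm is 20 / (1 − r²). For a standardised difference d, the noncentrality is d × √(20/2) / √(1 − r²).

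| r | Variance cut | Effective n per arm | Noncentrality, d = 0.8 | Power, d = 0.8 |
|---|---|---|---|---|
| 0 | 0% | 20 | 0.8 × 3.162 = 2.53 | about 69% |
| 0.3 | 9% | 20 / 0.91 = 22.0 | 2.53 / 0.954 = 2.65 | about 72% |
| 0.5 | 25% | 20 / 0.75 = 26.7 | 2.53 / 0.866 = 2.92 | about 80% |

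The powers come from simulation with t-based tests. The normal approximation runs 2 to 4 points higher (72%, 76%, 83%) with the same pattern. At r = 0.5 the confidence interval is narrower by 1 − √0.75 = 13%.

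**2. Chance imbalance.** If baseline NIHSS has an SD of 5, the standard error of the difference in means is 5 × √(2/20) = 1.58. A gap of 2 points or more is then 2 / 1.58 = 1.26 standard errors, which occurs by chance in about 21% of trials.

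**3. The pre-test.** The planned rule was simulated as: Mann–Whitney if either arm rejects normality, otherwise the t test. The article does not say whether the Lilliefors correction is used, so both versions were run on lognormal volumes.

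| Scenario | Rule, Lilliefors | Rule, uncorrected | Log-scale t |
|---|---|---|---|
| Log-SD 1.25, 60% reduction | 59% | 58% | 62% |
| Log-SD 0.75, log shift 0.6 | 67% | 62% | 69% |
| Log-SD 0.75, volume halved | 79% | 75% | 81% |

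Against a log-scale t test, the loss runs from 69 − 67 = 2 to 69 − 62 = 7 points. A fixed Mann–Whitney has 59% power in the first scenario and 79% in the third, so against it the loss runs from 0 to 79 − 75 = 4 points. Type I error of the rule was between 5% and 6%.

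**4. Ordinal against dichotomised mRS.** The control distribution was set to the 46% independence and 15.3% mortality cited in Background; the rest of its shape is assumed.

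| Common odds ratio | Mann–Whitney on full mRS | Chi-square, 0–2 | Fisher, 0–2 |
|---|---|---|---|
| 2.27 (46% to 66%) | 28% | 22% | 15% |
| 3 | 48% | 37% | 27% |

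The full scale carries more information, but power stays below 50% either way. For 46% against 66%, 80% power on mRS 0–2 would need 96 per arm.

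**The case against.** The case for leaving the plan alone is substantial, and most of it stands.

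- **This is a pilot with a safety primary outcome and no claim of efficacy power.** A reader might infer that the analysis throws away power and balance. The documents do not support that. Randomisation keeps the crude comparisons unbiased, and adjustment would correct only chance imbalance. The low power comes mainly from 40 patients.
- **The pre-test does little numerical harm.** A reader might infer that skewed infarct volumes would often go to a raw t test where it performs worst, at 36% power against 62% on the log scale (log-SD 1.25, 60% reduction). That is not the planned analysis. The plan sends non-normal data to Mann–Whitney, and the planned rule has 58–59% power there. With Lilliefors, at least one arm rejects normality 99% of the time in that scenario.
- **mRS 0–2 is a legitimate, interpretable endpoint.** It matches the 46% benchmark in Background. Choosing it is not an error.
- **A fuller protocol or SAP may add adjusted models.** Admission scores are recorded for later analysis, so it cannot be said that they will go unused.

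The last point does not dispose of the matter. The article does more than stay silent: it names specific crude tests and a gate that comes before any other analysis. That stated choice can be improved with data already in hand, and the phase-2 purpose gives a reason to do so.

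**Conclusion.** The point holds as a matter of efficiency and prespecification. The named tests give unbiased comparisons that are less precise than they need be. At an assumed correlation of 0.5 the avoidable variance is about 25% (power at d = 0.8 from about 69% to 80%). At 0.3 it is 9% and the gain is small (to about 72%). No document gives the true correlation, so the benefit is a range.

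The pre-test costs about 0 to 7 power points, depending on its version, the skew and the comparator, with type I error near 5%. The better reason to drop it is that the reported quantity depends on the data. Replacing mRS 0–2 is not justified; a shift analysis is useful support. None of this rescues inference at n = 40. Nor does it repair the separate rule in Statistical analyses that moves to phase 2 when no differences are found.

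**What to change.** Replace the normality and equal-variance gate with one prespecified method per outcome:

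- **Infarct volume:** ANCOVA of log volume on treatment, baseline NIHSS and ASPECTS, with a stated rule for zero volumes.
- **NIHSS:** comparison adjusted for its baseline value, with a rank-based ANCOVA named in advance if skew is expected.
- **mRS:** keep 0–2 at day 90 as the main efficacy measure. Add an ordinal shift across the full scale, adjusted for baseline NIHSS, as a supportive analysis.
- **Reporting:** give every estimate with a 95% confidence interval. Also report the residual SD and the baseline–outcome correlation, which an adjusted phase-2 design would need.

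If a fuller protocol or SAP already contains such models, align this section with it. The change is to wording only and needs no new data. It costs one or two degrees of freedom and a proportional-odds assumption for the shift summary.
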